### Participants

Persons meeting the criteria for the definition of a houseless person—someone who does not live in a building or "census houses," but rather in the open or seeks shelter in public places such as railway stations, under flyovers, places of worship, etc.—according to the 2011 Census of India, and residing in Chennai or Dhanbad, India during and after the Unlock 2.0 phase of the COVID-19 pandemic in India, aged >18 years will be recruited. Persons with a formal diagnosis of anxiety, depression, and any other mental illness will be excluded from the study and provided access to evidence-based treatments. All PEH availing the services of Samanjasa Foundation in Chennai and Dhanbad will be approached to participate in the study; the study information will be disseminated through the case workers. During earlier studies we found that this strategy ensures nearly 90% response rate; therefore, we are expecting a similar enrolment rate in this study as well. The participants will be divided into four groups—the Bhagavad Gita (Gita), Kuchipudi dance (Kuchipudi), both Bhagavad Gita and Kuchipudi dance (Both), and control groups—in a 1:1:1:1 ratio. The participant identification number, group assignment, four copies of a questionnaire with pre-filled participant ID and follow-up date, meeting schedule, and Zoom meeting link will be sealed in a small envelope and the envelopes will be placed in a fishbowl and shuffled. The participant ID will be generated in a random order by an independent statistician using a pseudo-random number generator script in Python 3.9.13. Group assignment will be generated in sequence by the independent statistician; the participant ID generated first will be associated with the Gita group, the second with the Kuchipudi group, the third with the Both group, the fourth with the Control group, the fifth with the Gita group, and so on. The project staff will fill and seal the envelopes with the respective contents. Once a participant provides written informed consent to participate in the study, they will be asked to pull an envelope from the fishbowl and not reveal its contents to the research team. They will also be instructed not to read the questionnaires until the sessions scheduled for the purpose of filling them out. To monitor and minimize the risk of contamination, especially given the potential for participants within the same community to communicate, the project staff will send weekly text messages to the participants regarding not sharing details about the intervention with anyone, including their family members. Additionally, the project staff will randomly contact three participants from each group via a phone call every two months and ask them if they had heard anything about the interventions in the other study groups. Furthermore, during community events and interactions, case workers will be asked to assess the level of knowledge regarding the intervention among the PEH. The participant journey is illustrated in Fig 1.

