### Interventions

The participants in the Gita group will be imparted the teachings of the second chapter of the Bhagavad Gita (all verses) for 1 week, for 60 minutes per day. The teachings of the Bhagavad Gita will be imparted by a trained teacher and the second chapter has been chosen as it is said to contain the essence of the entire Bhagavad Gita [16]. The participants in the Kuchipudi group will be taught the Kuchipudi dance choreography to a popular devotional song (“Sivashtakam”, choreographed by Padma Bhushan [name] [name], song duration is approximately 10 min) for 60 minutes per day by a trained teacher for 1 week. Every day for 1 week, the participants in the Both group will be taught the Kuchipudi dance choreography to a popular devotional song (“Vandanamu Raghunandana”, choreographed by Kala Tilakam [name], song duration is approximately 5 min), which is shorter in duration than the song used in the Kuchipudi group, for 30 minutes by a trained teacher, followed by imparting the teachings from selected verses of the second chapter of the Bhagavad Gita (Verse 40–72) for 30 minutes by a trained teacher. The participants in the control group will receive no intervention. The participants will be instructed to join their assigned groups at the scheduled meeting times using the meeting link in their sealed envelopes. Apart from the teaching sessions, meetings will also be scheduled one day before the start of the teaching sessions, one day after the end of the teaching sessions, 40 days after the end of the teaching sessions, and 1 year after the end of the teaching sessions for the purpose of recording the baseline, immediate post-intervention, delayed post-intervention, and long-term follow-up measurements, respectively. For participants in the control group, the meeting schedule will consist of only the four measurement sessions.

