### Outcomes and measures

The primary outcome is psychological distress measured by the Kessler scale of psychological distress (K10) in this study. The K10 is a 10-item questionnaire that measures psychological distress based on questions about anxiety and depressive symptoms. It has previously been used in research conducted with PEH [17, 18]. At the immediate post-intervention, delayed post-intervention, and long-term follow-up measurements, apart from the K10, the participants will be asked if they have continued practicing the techniques learned during the intervention (Kuchipudi group: continued practice of the choreography, Gita group: continued self-reflection on the teachings of the Bhagavad Gita, Both group: continued practice of the choreography and continued self-reflection on the teachings of the Bhagavad Gita, and control group: none). The study flowchart is presented in Fig 2.

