### Data collection and management procedures

During each scheduled measurement session, the participants will be asked to take the questionnaire they were provided with in the sealed envelopes given to them at the time of enrolment that is pre-filled with the date of the appropriate measurement session. They will then be asked to hold the questionnaire sheet with the date visible to the camera and trained research support staff will check that each participant is holding the correct questionnaire. They will then walk the participants through how to fill in the questionnaire. Once they confirm that the questionnaires have been filled, they will walk the participants through how to take a photograph of the sheet and send the photo to the staff member via WhatsApp. Once the staff member receives legible photographs of the filled questionnaires from all participants, the meetings will be ended. The project staff will then save the photographs into as portable document format files on a secure computer situated in the research office of our organization and print out the same for our records. Our organization’s policy is to store both soft and hard copies of all research material—the soft copies are stored for a period of 2 years and the hard copies are stored for a period of 10 years. The research team will have unrestricted access to the final dataset.

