## Blinding

The study will involve three separate teams—trained teachers, project staff, and the research team. Trained teachers will be responsible for administering the interventions; the teachers will be blinded to the K10 results. Project staff will be responsible for ensuring participant compliance, collecting the filled K10 questionnaires as photos via WhatsApp, and printing the photos and storing them until data analysis; project staff will be blinded to data analysis. The research team will be responsible for study design, participant recruitment, obtaining written informed consent, data analysis and reporting; the research team will be blinded to participant group allocation.

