### Risk mitigation strategy

As PEH are a vulnerable group, several risk mitigation strategies have been put in place to ensure the safety and wellbeing of the participants. These are as follows:

Informed Consent will be obtained from each participant, after providing them with oral and written information clearly explaining the purpose, procedures, potential risks, and benefits of the intervention. To ensure that the participants understand their rights, the voluntary nature of participation, and their ability to withdraw at any time without consequences, they will be asked to repeat the information in their own words, orally and in writing, to the research team.To facilitate compliance with the intervention, the project staff will be drawn from the volunteers who are involved in the day-to-day activities of our organization, engaging regularly with our PEH clients. The trained teachers who will administer the interventions will be from external organizations; this will help the participants engage with organizations other than our own, thus deepening their engagement with civil society. To maintain objectivity and minimise the possibility that the participants may feel coerced to participate in the research on account of being approached by volunteers they frequently engage with, the research team is kept separate from the client engagement teams in our organization.Secure online platforms will be used in adherence to data protection regulations of our organization to safeguard personal data of all stakeholders. The smartphones used for sending and receiving correspondence and photographs of the filled K10 questionnaires will be those provided by the organization. The project staff will not use their personal phone numbers for communication with the participants under any circumstance.Keeping the culture of India in mind, the participants will be asked to provide oral consent from their next of kin. This will be recorded on the consent forms and countersigned by the participant. In case the participant is unable to read or sign their name, the consent process will be conducted in the presence of two healthcare professionals who are not related to our organization. A blank informed consent form in English and Hindi has been provided as S1 File. The informed consent forms in other languages (Tamil, Telugu, and Bengali) are true translations of the informed consent form in English.The participants’ technological access and proficiency will be assessed at the time of obtaining consent to ensure that they can fully engage with the online intervention. In case technological proficiency needs to be improved, digital literacy training and training on the digital platforms to be used in the intervention will be provided.

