## Strengths and limitations of this study

The study takes into account the complex impact of the coronavirus disease pandemic on mental health among people experiencing homelessness (PEH), addressing a timely and critical need. The incorporation of both a traditional emic intervention (Bhagavad Gita teachings) and a hobby-based positive control (Kuchipudi dance) demonstrates a multifaceted approach to enhancing coping mechanisms for PEH. Furthermore, the involvement of a Non-Governmental Organization with a history of dedicated support for PEH lends credibility and ensures the study is grounded in real-world experiences and needs. While the Kessler scale is a validated tool for assessing psychological distress, relying solely on self-report measures could introduce response bias and potential inaccuracies due to participants’ subjective interpretations. Moreover, the emic intervention involving the Bhagavad Gita teachings might not be universally applicable to all PEH due to cultural differences and varying beliefs, potentially impacting the intervention’s effectiveness and relevance.

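### The self-reported K10 is collected with help from staff who are not blinded to allocation and have several ways of knowing a participant's arm

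*Protocol article*

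**What the plan says.** All places are in the protocol article.

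- **Outcomes and measures:** "The primary outcome is psychological distress measured by the Kessler scale of psychological distress (K10) in this study". At the three post-intervention measurements, participants are also asked whether they have kept up what they were taught. What is asked about differs between the three intervention arms, and the control arm has nothing to report.
- **Data collection and management procedures:** at each session "trained research support staff will check that each participant is holding the correct questionnaire". Then "They will then walk the participants through how to fill in the questionnaire", after which they explain how to photograph the sheet and send it by WhatsApp.
- **Blinding:** three teams are named: teachers, project staff and the research team. Project staff oversee compliance and collect the completed K10 forms. Of them it says that "project staff will be blinded to data analysis". Only the research team is described as blinded to allocation.
- **Participants:** "The project staff will fill and seal the envelopes with the respective contents". Every two months project staff also telephone three randomly chosen members of each group to check for contamination.
- **Interventions:** participants are told to "join their assigned groups at the scheduled meeting times using the meeting link in their sealed envelopes". Control participants have the four measurement meetings and no others.
- **Risk mitigation strategy:** project staff come from volunteers in regular contact with the clients. On literacy: "In case the participant is unable to read or sign their name, the consent process will be conducted" before two outside healthcare professionals.
- **Strengths and limitations of this study:** "relying solely on self-report measures could introduce response bias".

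**The concern.** Participants know their arm, so the K10 cannot be protected by blinding the respondent. What remains is the setting and the person who administers the form. The plan gives that role to a team that is not said to be unaware of allocation, that is responsible for getting participants to follow the interventions, and that belongs to the organisation running the trial and already knows the respondents.

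If help or encouragement at the session differs by arm, even unintentionally, the difference enters the K10 directly and cannot be told apart from a treatment effect. A larger sample does not reduce it. The Risk mitigation section recognises that familiarity with the volunteers could make people feel pressed to take part, and for that reason keeps the research team apart from the client-facing teams. It offers no comparable protection for outcome measurement.

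**Working it through.** The protocol states no figure on this point, so the check compares its sections.

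**1. Who collects the K10?** The Blinding section says project staff. The data collection section has the session run by research support staff, a label that is not among the three teams, and then has project staff save the photographs. Reading the two as the same people is natural but not explicit.

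**2. What are they blinded to?** Data analysis only. The Blinding section lists blinding team by team, so this is what the plan states and not a detail left out of a condensed article.

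**3. Can they know an individual's arm?** There are four routes, strongest first:
- The contamination calls sample three people per group, which requires a link from person to arm.
- The continued-practice question is arm-specific and is asked at the same three sessions as the post-intervention K10. Asking it or receiving the answer can show the arm.
- Project staff send reminders before scheduled meetings (Plan for handling missing data and protocol deviations). Control participants have only four meetings, so the reminder schedule identifies them.
- Participants join by a group link. Measurement meetings held by arm are the likely reading, although the text does not say so outright.

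**4. What about participants who cannot read?** They are foreseen in the consent procedure, and the eligibility criteria do not exclude them. The K10 is a written sheet. The protocol does not say how they complete it or who helps; the outside professionals are mentioned for consent only.

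**5. Would a planned analysis detect it?** The sensitivity analyses cover imputation method, alternative models, outliers and contamination. None concerns how the K10 was obtained.

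**6. Scale, as illustration only.** Suppose there is no true effect and reporting differs between two arms by b points. For a two-sided test of two means with n = 54 per group (Sample size calculation):

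- SE = SD × √(2/54) = 0.1925 × SD
- Rejection probability = Φ(−z + b/SE) + Φ(−z − b/SE)

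The protocol gives no K10 SD, so 5 to 13 is assumed. The upper end is about the SD at which 54 per group gives 80% power for the protocol's 7 points: 7 / (0.1925 × 2.80) ≈ 13.

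Worked case, SD 10 and b = 2: SE = 1.925, b/SE = 1.039, and Φ(−0.921) + Φ(−2.999) = 0.179 + 0.001 = 18.0%.

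| Assumed shift b | SD 5 | SD 7 | SD 10 | SD 13 |
|---|---|---|---|---|
| 1 point, α = 0.05 | 18.0% | 11.5% | 8.1% | 6.8% |
| 2 points, α = 0.05 | 54.7% | 31.8% | 18.0% | 12.6% |
| 2 points, α = 0.05/3 = 0.0167 | 37.6% | 18.2% | 8.8% | 5.6% |

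The last row applies Bonferroni over the three comparisons with control. The table shows that a shift well below 7 points would matter if it occurred. It is not evidence that one occurs.

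**The case against.** The strongest reply is that the text describes help with a form and nothing more. Staff explain how to fill in the sheet and, in the same terms, how to photograph it. Participants write their own answers, the analysts are blinded to allocation, the teachers are external, and a session manual is something a condensed article may leave to the full protocol. Much of this stands, and it rules out several stronger readings that a reader might infer:

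- **Staff coach the answers.** Nothing says they read items aloud, explain them or hear responses.
- **Non-readers depend on staff for their answers.** Inability to read is mentioned only for consent, and the number of such participants is not given. What can be said is that their route to completing the K10 is not described.
- **Packing the envelopes unblinds staff.** The sealed envelopes are shuffled and each participant draws one, so packing does not show who received which arm unless a link from ID to group is kept. The routes in step 3 of the working carry the argument.
- **The bias favours the Gita arm.** Kuchipudi classes are among the organisation's own usual activities, so no direction is shown, least of all for Gita against Kuchipudi.
- **The education subgroup is confounded by mode of administration.** No difference in mode by literacy is documented, and one that was equal across randomised arms would not by itself bias the arm comparison.

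The reply does not remove the central fact. Blinded analysts do not protect an outcome that is recorded before it reaches them, and the stated blinding does not cover the people who collect it.

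**Conclusion.** The point holds in a limited form. The plan assigns collection of its self-reported primary outcome to staff who are not stated to be blinded to allocation, who have compliance duties, who are drawn from volunteers in regular contact with the clients, and who can learn individual arms by several documented routes. Arm-dependent influence on the K10 is possible and unaddressed. The limitations section admits response bias in general but not this source.

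Size and direction cannot be derived from the documents. The rejection rates above rest on assumed shifts, assumed SDs and a simple two-group comparison, not the planned GEE. The conclusion also relies on two readings that are likely but not explicit: that the research support staff are project staff, and that measurement meetings are held by arm. The contamination calls and the practice question support it without the second reading. This is an inexpensive improvement to outcome ascertainment, not a demonstrated bias.

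**What to change.** 1. In the data collection and Blinding sections, name one team for K10 collection. Draw it from existing staff who do not handle compliance, contamination calls or group-specific reminders.
2. Give these staff measurement-session links under neutral codes and do not tell them the arm.
3. Limit their help to a fixed form-handling script. Where a participant needs the form read aloud, read it verbatim, in the same way in every arm, and record that this was done.
4. Ask the continued-practice question only after the K10 photograph has been received, on a separate sheet or through other staff. Without this step the question can unblind the collectors before the K10 is complete.
5. State the K10 collectors' allocation status in the Blinding section. In the limitations, state that participants are unblinded and may reveal their arm.

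The cost is a division of duties, a short script and one recorded item. Staffing on measurement days becomes less flexible; the protocol gives no staff numbers, so the sponsor must confirm that the split is feasible. Blinding of the collectors will remain incomplete where participants disclose their arm.

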### Statistical methods

#### Data analysis

All results will be reported in accordance with the CONSORT guidelines to ensure comprehensive and transparent reporting of the trial’s outcomes. Descriptive summaries of baseline characteristics will be presented to provide an overview of the study population. The comparisons will be between each intervention group and the control group, as well as within each intervention group over time. The repeated measures data will be analysed using the generalised estimating equation (GEE) framework. For the analysis of the primary outcome using the GEE framework, robust standard errors will be used to account for correlated data. Pairwise post-hoc comparisons will be conducted to identify specific group differences. To control for the risk of type I error in these multiple comparisons, the Bonferroni correction will be applied. Subgroup analysis will be conducted using analysis of covariance (ANCOVA) or non-parametric ANCOVA [19] depending on the normality of the data; this may include stratification by age, educational attainment, religion, and employment status. Multiple comparisons will also be addressed using appropriate statistical corrections. These may include the Bonferroni correction, Holm’s adjustment, or the Benjamini-Hochberg procedure, depending on the specific comparisons and the number of tests conducted. The data analysis will be conducted using Python 3.9.13. Statistical significance will be set at a two-tailed p < 0.05.

#### Sample size calculation

The required sample size for GEE was calculated using the formula,

$$n=[(Z\alpha /2+Z\beta {)}^{2}*V\_eff]/(\Delta^{2}*\rho^{2}),$$

where n is the required sample size per group; Zα/2 is the critical value of the standard normal distribution for a two-tailed test with a significance level of α; Zβ is the critical value of the standard normal distribution for a specified power (1-β) of the test; V_eff is the effective sample size, which accounts for the correlation between the repeated measures within individuals; Δ is the minimum clinically significant difference; r is the number of repeated measures; and ρ is the correlation between the repeated measures.

Assuming a conservative value of 0.5 for ρ based on previous literature [20, 21], and for an α of 5%, 1-β of 80%, r of 4, and Δ of 7 [22, 23], we can calculate the effective sample size as follows:

$$\begin{array}{l} V\_eff=n/(1+(r‐1)*\rho )\\ \;=55/(1+(4‐1)*0.5)\\ \;=22.5 \end{array}$$

Therefore, n can be calculated as follows:

$$\begin{array}{l} n=[(1.96+0.84{)}^{2}*22.5]/(7^{2}*0.5^{2})\\ \;=53.3 \end{array}$$

Thus, at least 54 participants per group must be enrolled to have 80% power to detect a minimum clinically significant difference of 7 points between the groups using GEE, with a significance level of 5%. As there are four groups in the study, a total of 216 participants (54 per group) must be enrolled. Based on our previous experience, a dropout rate of 16% was expected; to account for this, we aim to recruit a total of 256 participants, with 64 participants per group.

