Does continued practice influence the effect of the interventions in people experiencing homelessness	The decrease from baselines to delayed post-intervention and long-term follow-up Kessler psychological distress scale scores will be significantly larger in all intervention groups in participants who continue the practices learned during the intervention compared to that in participants who do not continue the practices learned during the intervention	54 participants each in the Bhagavad Gita group, Kuchipudi dance group, Both Bhagavad Gita and Kuchipudi dance group, and Control group for 80% power and 5% alpha	Participants in each group will be subdivided based on whether or not they continued practice during each follow-up. Repeated measures analysis of variance will be conducted on the subgroups	If our hypothesis holds true, it would suggest that sustained practice contributes to greater psychological well-being. Conversely, if there are no significant differences in the decrease of the Kessler psychological distress scale scores between participants who continue and those who do not continue the practices, it would indicate that continued practice does not play a significant role in the effectiveness of the interventions

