### Primary analysis

GEE Framework: The primary outcome, psychological distress as measured by the K10 scale, will be analyzed using the GEE framework. Robust standard errors will be used to account for correlated data due to repeated measures. An exchangeable correlation structure will be assumed.Primary Comparisons: Comparisons will be made between each intervention group (Gita, Kuchipudi, and Both) and the control group. Within each intervention group, comparisons over time (pre-intervention, immediate post-intervention, 40 days post-intervention, and 1-year post-intervention) will be performed.Pairwise Post-Hoc Comparisons: Pairwise post-hoc comparisons will be conducted following significant GEE results to identify specific group differences. The Bonferroni correction will be applied to control for the risk of type I error in these multiple comparisons.

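### The sample-size calculation does not yield its stated result (its own inputs give 14.4, not 53.3), is circular and contains no K10 standard deviation, so the 80% power claim is unsupported

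*Protocol article*

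**What the plan says.** The Sample size calculation section gives a formula described as being for GEE: n = (Zα/2 + Zβ)² × V_eff / (Δ² × ρ²). It says that "V_eff is the effective sample size, which accounts for the correlation between the repeated measures within individuals", and computes it as n/(1+(r−1)ρ). The inputs are two-sided alpha 5%, power 80%, r = 4, Δ = 7 and ρ = 0.5, the last introduced as "Assuming a conservative value of 0.5 for ρ based on previous literature". With n = 55 inserted, V_eff is printed as 22.5 and the resulting n as 53.3. From this the section concludes, for a between-group difference, that "at least 54 participants per group must be enrolled to have 80% power to detect a minimum clinically significant difference of 7 points". The total of 216 follows, and with 16% dropout the recruitment target is 256 (64 per group).

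Table 1 in the Introduction repeats "54 participants each in the Bhagavad Gita group, Kuchipudi dance group, Both Bhagavad Gita and Kuchipudi dance group, and Control group for 80% power" in the sampling plan of all four research questions. One of these is the third row, where each group is subdivided by whether participants continued to practise.

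The Primary analysis section lists three comparisons with control. It then lists pairwise post-hoc comparisons following significant GEE results, for which "The Bonferroni correction will be applied to control for the risk of type I error in these multiple comparisons".

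**The concern.** The figures 54, 216 and 256 are the only justification of the trial's size, and all come from this one calculation. If it fails, a reader cannot tell what difference the trial was able to detect. This matters most in Table 1's continued-practice row, which says in advance that a non-significant difference would indicate that continued practice plays no significant role. That reading needs real power behind it.

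This is not a detail that a journal article leaves to a fuller document. The article prints the whole calculation, defines every term and draws its conclusion from it.

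**Working it through.** **Inputs, all from the Sample size calculation section:** Zα/2 = 1.96, Zβ = 0.84, r = 4, ρ = 0.5, Δ = 7, n inserted = 55, V_eff printed = 22.5, result printed = 53.3.

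**1. Reproducing the printed figures.**
- V_eff = 55/(1 + 3×0.5) = 55/2.5 = 22.0 (printed 22.5).
- n = (1.96+0.84)² × 22.5/(7² × 0.5²) = 7.84 × 22.5/12.25 = 176.4/12.25 = **14.4** (printed 53.3).
- With V_eff = 22.0: 7.84 × 22/12.25 = 14.1.
- To obtain 53.3, V_eff would have to be 53.3 × 12.25/7.84 = 83.3.

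Simple slips do not recover 53.3. Leaving Δ and ρ unsquared gives 176.4/3.5 = 50.4. A two-sample factor of 2 gives 28.8, and a factor of 4 gives 57.6. Using 55 in place of V_eff gives 35.2.

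**2. Circularity.** Substituting V_eff = n/2.5 gives n = 7.84 × (n/2.5)/12.25 = 0.256n. Only n = 0 satisfies this. Iterating from 55 gives 14.1, 3.6, 0.9 and so on towards zero. Correcting the arithmetic therefore does not rescue the method.

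**3. Missing variance.** Power for a difference in points needs the outcome's SD. V_eff occupies the place of a variance but is defined as a sample size, and no K10 SD or variance appears anywhere in the document. The formula also divides by ρ², so a larger ρ reduces n through both terms and ρ = 0 leaves n undefined. Whether 0.5 is conservative cannot be judged from it.

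**4. What 54 per group could detect (illustration).** Assume a two-group comparison of means at one time point, no baseline adjustment and 80% power. The detectable difference in SD units is (z for alpha + 0.84) × √(2/54), and the largest SD for which 7 points reaches 80% power is 7 divided by that. The protocol does not state the number of Bonferroni tests, so 3 and 6 are assumptions.

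| Two-sided alpha | Detectable difference | Largest SD for 7 points |
|---|---|---|
| 0.05 | 0.54 SD | 13.0 |
| 0.05/3 (assumed) | 0.62 SD | 11.2 |
| 0.05/6 (assumed) | 0.67 SD | 10.5 |

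Under the same simplification, with n per group = 2(z for alpha + 0.84)² × SD²/7²:

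| Assumed SD | n per group at 0.05, 0.05/3, 0.05/6 | Power with 54 at 0.05, 0.05/3, 0.05/6 |
|---|---|---|
| 10 | 33, 43, 50 | 95%, 89%, 84% |
| 13 | 55, 73, 84 | 80%, 66%, 56% |

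**5. Table 1, continued-practice row.** Suppose 54 v 54 had exactly 80% power at 5%. An assumed even split of one group into 27 v 27, the most favourable split of 54, would have power Φ(2.80 × √0.5 − 1.96) = Φ(0.02), about 51%.

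**The case against.** The arithmetic, the circularity and the missing SD are not open to a serious defence. The inputs, the symbolic formula and the numeric lines agree with one another and only the results are wrong, so faulty text extraction does not explain it. The fair objections concern how far the point reaches.

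- **A reader might infer that the trial is underpowered.** The document does not show this. At an assumed SD of 10, 54 per group exceeds 80% power for 7 points even at 0.05/6. Nor is 14.4 a usable sample size, because it comes from the same invalid formula.
- **A reader might infer that the plan tests its main contrasts at 0.05/6.** Bonferroni is attached to the pairwise post-hoc comparisons. Neither the number of tests nor whether the three control contrasts are covered is stated. What stands is narrower: the calculation uses unadjusted 5% although a correction is planned for some group contrasts.
- **A reader might take an SD of 13 as a hard limit.** It holds only for the simplified comparison above. At ρ = 0.5, baseline adjustment at one visit multiplies the variance by 1 − 0.25 = 0.75. The limit then rises from 13.0 to 13.0/√0.75 = 15.0 at 5%, and from 10.5 to about 12 at 0.05/6. Averaging over visits would raise it further.
- **A reader might think the subgroup analyses also claim 80% power.** They do not. In the other three rows of Table 1 the claim belongs to the main question, and subgroups are given separate post-hoc power analyses.

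A null result could also still be read from its confidence interval. That is true, but it does not repair the stated power.

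**Conclusion.** The calculation is wrong as written and cannot produce a sample size by its own method. The printed inputs give 14.4 (or 14.1), not 53.3; n is an input to itself; and no SD enters. The claim of 80% power for 7 points with 54 per group is therefore unsupported. Whether true power is above or below 80% depends on a K10 SD that the document does not give, on the contrast and time point, and on the alpha finally used.

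Two further points stand in limited form: the unadjusted alpha, and the power claim in Table 1's continued-practice row, which the calculation does not address. The figures for 3 and 6 tests, the SDs of 10 and 13 and the 27 v 27 split are assumptions for illustration, not estimates for this trial.

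**What to change.** Delete the equation and its worked lines. Keep the recruitment target of 64 per group, which at 16% dropout leaves 64 × 0.84 = 53.8, about 54 evaluable. State the power, or the detectable difference, for 54 evaluable per group using:

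- an explicit K10 SD with its source;
- a named contrast and time point, and whether baseline or repeated measures are used, with the assumed correlation;
- the alpha that will be applied, including the number of Bonferroni tests and whether the control contrasts are among them.

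Remove the 80% power statement from the continued-practice row of Table 1.

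The cost is wording only, with no change to recruitment. The stated power may become less favourable if the sourced SD is large. In the simple illustration, an SD of 13 at 0.05/6 would need 84 per group, more than the 64 to be recruited. In that case the article should report the lower power.
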